## Abstract

**Background:**

In Cambodia, HIV prevalence is concentrated in key populations including among female entertainment workers (FEWs) who may engage in direct or indirect sex work. Reaching FEWs with sexual and reproductive health (SRH) services has been difficult because of their hidden and stigmatized nature. Mobile-phone-based interventions may be an effective way to reach this population and connect them with the existing services. This article describes study design and implementation of a randomized controlled trial (RCT) of a mobile health intervention (the *Mobile Link*) aiming to improve SRH and related outcomes among FEWs in Cambodia.

**Methods:**

A two-arm RCT will be used to determine the effectiveness of a mobile-phone-based text/voice messaging intervention. The intervention will be developed through a participatory process. Focus group discussions and in-depth interviews have been conducted to inform and tailor behavior change theory-based text and voice messages. During the implementation phase, 600 FEWs will be recruited and randomly assigned into one of the two arms: (1) a control group and (2) a mobile phone message group (either text messages [SMS] or voice messages [VM], a delivery method chosen by participants). Participants in the control group will also receive a weekly monitoring survey, which will provide real-time information to implementing partners to streamline outreach efforts and be able to quickly identify geographic trends. The primary outcome measures will include self-reported HIV and sexually transmitted infections (STI) testing and treatment, condom use, contraceptive use, and gender-based violence (GBV).

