### Sampling and participant recruitment

We will use a stratified random sampling method to recruit survey participants. Venues will be selected from a list of all entertainment venues in the study sites based on a recent report on geographic information system (GIS) mapping of HIV key populations in Cambodia [47]. They are matched with 30 similar venues and then randomized for size and type of the venues. We will continue to sample from our list of all entertainment venues until we have a total of 600 FEWs recruited. All enrolled participants will complete an informed consent and a baseline questionnaire survey. Next, one venue from each venue pair will be randomly assigned to the intervention group: VM or SMS (1) and the other to the control group (0) with standard of care (no additional mobile phone-based SRH support) with a 1:1 venue allocation ratio. Both groups will be followed for one year, and a six-month and 12-month questionnaire will be administered by trained data collectors (see Fig. 3).

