#### Phase II: Intervention

The *Mobile Link* intervention comprises a series of automated SMS/VMs to participants’ mobile phones over the 12-month period. Participants will receive the first message within the first day of the intervention. The messages will be designed to enhance and increase utilization of existing HIV and SRH services by reminding clients about safe sex methods available to them and providing a conduit for additional support. Upon enrollment into the study, participants in all groups will receive a face-to-face baseline behavioral survey conducted by a data collection team who remained masked to intervention allocation at enrollment.

The baseline questionnaire (see Additional file 5) was designed by the study team using sections from standard questionnaires currently in use at KHANA for assessing similar measures in populations of high-risk women in Cambodia. The questionnaire was created in English, translated to Khmer, and back-translated to English. The questionnaire will be pilot tested with 15 FEWs similar in eligibility to future study participants using cognitive interviewing techniques [48]. Next, participants will be randomized into intervention and control groups: Group 0 is the control group and Group 1.1 and 1.2 are the intervention group (1.1 = SMS [1.1a Khmer characters or 1.1b Romanized Khmer] or 1.2 = VM in Khmer).

Those in the control group will get one “check-in” SMS or VM between baseline and midline and another between midline and endline. Participants will be asked to confirm receipt of this message. These messages will contain no health information and will be used as a way to stay in touch with participants and to compare “receipt confirmation” rates to the intervention group. All participants will be asked to choose whether they would prefer to receive SMS or VM and their reason for their choice. If they choose SMS, they will be asked if they prefer Khmer characters or Romanized Khmer. Recent studies on choosing the method for receiving interventions during an RCT have demonstrated that it may increase participation and retention [49].

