A message schema was developed in which each participant will receive a message from a different topic group each week for 10 weeks. The messages will tend to follow a flow of rights-based health information and then linkage (though there is some variance depending on topic). However, after each message, participants will also have the option to be linked to an outreach worker. After the tenth week, the topic areas will cycle through again, but the messages within the topic areas will be unique. After weeks 30, 40, and 50 (+ 2), messages will be repeated to reinforce particular concepts and ideas. Participants who indicate they would like to talk to a counselor will receive a call from a *Mobile Link* staff. The counselor will provide individualized information via telephone or face-to-face on that particular topic and, if needed, can escort the participant to receive the required services.

Participants will also receive a weekly 5–7-question survey that asks about more common and/or time-sensitive issues such as STI symptoms, vaginal infection/irritation, support for GBV, or psychological issues. Once a month, participants will be asked if they are using contraception and/or want to be linked to family planning counseling. Participants who endorse any of the survey questions will be asked if they want to be linked to an outreach worker. Therefore, it is important to note that, while the topics in the messages will change each week—as well as the topical prompts for linkages to outreach workers—the weekly monitoring survey provides another consistent and constant platform for mobile linkage.

Trained data collectors and community health workers in the selected sites will deliver the *Mobile Link* intervention. SMS/VM are scheduled and sent using the open-source software program developed by InSTEDD (instedd.org). InSTEDD and the Project Coordinator will retain data on the SMS/VM messages sent, responses to messages, and outcomes of follow-up phone calls.

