#### Control group

Participants in the control group will receive the current existing standard of care, but not the health-related SMS/VMs or associated follow-up phone calls. Standard of care consists of access to existing HIV and SRH services which includes: face-to-face counseling; free HIV and STI testing and condoms; and clinic phone numbers and hotline phone numbers with a toll-free help line for clients staffed by trained counselors. Control group members will receive “check-in” reminder calls before questionnaire appointments (midline and endpoint).

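### The protocol contradicts itself on whether controls receive the weekly survey, which as described carries an offer of linkage to an outreach worker

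*Protocol article*

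**What the plan says.** **Abstract, Methods paragraph.** "Participants in the control group will also receive a weekly monitoring survey". Its stated use there is to give implementing partners current information for their outreach work.

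**Sampling and participant recruitment.** Control venues are assigned "standard of care (no additional mobile phone-based SRH support").

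**Phase II: Intervention, on controls.** Controls get one check-in "SMS or VM between baseline and midline and another between midline and endline". On content: "These messages will contain no health information and will be used as a way to stay in touch with participants". They also serve to compare receipt confirmation with the intervention group.

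**Control group.** Controls get existing standard care, "but not the health-related SMS/VMs or associated follow-up phone calls", plus reminder calls before the midline and endpoint questionnaires.

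**Phase II: Intervention, on the survey.** "Participants will also receive a weekly 5–7-question survey". The arm is not named. The survey covers matters such as STI symptoms, vaginal infection, support after gender-based violence (GBV) and psychological problems, with a monthly contraception question. A woman who endorses any item is asked whether she wants to be put in touch with an outreach worker. The section concludes that "the weekly monitoring survey provides another consistent and constant platform for mobile linkage".

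**Comparators.** Objective 3 compares Mobile Link with the implementing organization's standard services. Phase III: Cost-effectiveness analyses defines the ICER against having no message intervention at all.

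**The concern.** The article gives two accounts of what the control arm receives, and no section reconciles them. The difference matters because the survey, as described, does more than collect data: it asks about symptoms and needs and then offers a route to services. Several primary outcomes (STI screening and treatment, contraceptive use, GBV) lie on the path that such an offer is meant to influence, and use of a peer counselor is a secondary outcome.

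The two accounts define different treatment contrasts. In one, the whole package is compared with standard care. In the other, messages are added to survey-based linkage that both arms receive. Under the second, a null result could mean that Mobile Link does nothing, or that the component shared by both arms did the work. A claim of effectiveness or cost-effectiveness against standard care would not follow from that design.

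**Working it through.** The document gives no figure to reproduce here. The check is a comparison of texts, a count of contacts, and a short argument on what can be derived.

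**1. Which sections give controls the weekly survey?**

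- Abstract: yes, naming the control group.
- Sampling and participant recruitment: not mentioned; no added phone-based sexual and reproductive health (SRH) support.
- Phase II: Intervention, control paragraph: not mentioned; two check-ins.
- Control group: not mentioned; standard care plus reminder calls.
- Phase II: Intervention, survey paragraph: arm not named.

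**2. Can one reading make all five agree?**

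- *The survey paragraph covers both arms.* It then agrees with the abstract. But a phone survey that offers linkage to SRH services is added phone-based SRH support, which the sampling section rules out. Two check-ins to stay in touch would also have little purpose for women contacted every week.
- *The survey paragraph covers the intervention arm alone.* It then agrees with the three control descriptions, but the abstract, which names the control group, is wrong as written.
- *Controls receive a survey without the linkage offer.* No section describes such a survey.

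The eligibility criterion of willingness to receive two messages a week for a year does not settle the matter. It applies to every woman before allocation.

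**3. Contacts in dispute.** Inputs: 12 months taken as 52 weeks, consistent with the message schedule running to week 50 plus 2; 300 women per arm; 5–7 questions per survey; two check-ins. Face-to-face surveys and appointment reminders are excluded.

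- Per control woman with the survey: up to 52 surveys, or 52 × 5 = 260 to 52 × 7 = 364 questions.
- Per control woman from the check-ins: 2.
- Control arm: at most 52 × 300 = 15,600 surveys, against 2 × 300 = 600 check-ins.

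Linkage is offered only after an item is endorsed, and the document gives no endorsement rate. The number of offers therefore cannot be derived.

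**4. Effect on the contrast.** Assume additive effects, with *m* for messages and *s* for survey-based linkage.

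- Survey in the intervention arm only: contrast = *m* + *s*.
- Survey in both arms: contrast = (*m* + *s*) − *s* = *m*.

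The share removed is *s*/(*m* + *s*). The document gives neither *m* nor *s*, so its size is unknown.

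**5. Effect on the ICER.** Let *C_m* and *C_s* be the costs of the two components.

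- Survey in the intervention arm only: ICER = (*C_m* + *C_s*)/(*m* + *s*).
- Survey in both arms: ICER = *C_m*/*m*, because the survey cost also falls in both arms.

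For positive *m* and *s*, the second exceeds the first exactly when *C_m*/*m* > *C_s*/*s*. No component costs are given, so the ICER could rise, stay the same or fall.

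**The case against.** The best defence is that the abstract contains a slip. The three body sections on the control arm agree with one another, the survey is described under the intervention heading directly after the message schedule, and objective 3 and the ICER both presuppose a standard-care comparator. One sentence dissents, and correcting it might be enough. This is plausible, but the sentence names the control group and the survey paragraph names no arm, so a reader cannot establish from the text that it is a slip.

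It can also be said that the abstract presents the survey as a monitoring tool and mentions no linkage offer to controls, and that the survey is one linkage channel among several, since each message also carries a linkage option. Both are fair. That controls would receive the offer is an inference from joining the abstract to the survey paragraph, and the survey is not the whole of the intervention.

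Some stronger readings do not stand:

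- A reader might infer that controls get nothing beyond two check-ins. Phase II never says so, and the Control group section adds reminder calls. The conflict rests on the three control descriptions taken together.
- A reader might treat 15,600 as the number of linkage offers reaching controls. It is a ceiling on surveys sent.
- A reader might put a figure on lost power, or say that the cost per extra outcome would double. A power figure needs an assumed effect and an assumed split between components, and must allow for allocation by venue. The doubling claim holds incremental cost fixed while halving the effect, although the survey cost would also fall in both arms.

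**Conclusion.** The contradiction is real and goes beyond wording, because it determines what the comparator arm receives. The stated comparators for objective 3 and the ICER fit only a control arm without the survey. If controls receive the survey with its linkage offer, any effect of that component drops out of the between-arm contrast, and the trial addresses the added value of messages.

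The size that can be stated is the exposure: up to about 52 surveys per control woman over 12 months, compared with two check-ins. The size of any dilution and the direction of any change in the ICER cannot be obtained from this document. The conclusion does not depend on which account is intended, and the review does not choose between them; that is for the sponsor to state.

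**What to change.** Before recruitment, which the Trial status section says has not started:

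1. Reconcile the abstract, Sampling and participant recruitment, both parts of Phase II: Intervention, and Control group. List each phone contact once (messages, weekly survey, linkage offer, check-in, reminder) with the arm or arms that receive it. This would also settle whether the check-ins are messages between surveys, as in Phase II, or reminder calls, as in Control group.
2. In the survey paragraph of Phase II, name the arm or arms receiving the survey and the linkage offer.
3. Word objective 3, the ICER comparator and the trial's conclusion to match the control condition that the sponsor states. A claim against standard care fits only if controls receive no survey-based linkage. Otherwise the claim is for messages added to such linkage.
4. Report by arm the survey responses and outreach linkages that Additional analyses already plans to describe.

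The cost is mainly drafting. Sent messages, responses and follow-up call outcomes are already to be retained, so the by-arm report should need no new data collection.

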**Discussion:**

If the *Mobile Link* trial is successful, participants will report an increase in condom use, linkages to screening and treatment for HIV and STI, and contraception use as well as a reduction in GBV. This trial is unique in a number of ways. First, the option of participation mode (SMS or VM) allows participants to choose the message medium that best links them to services. Second, this is the first RCT of a mobile-phone-based behavior change intervention using SMS/VMs to support linkage to SRH services in Cambodia. Lastly, we are working with a hidden, hard-to-reach, and dynamic population with which existing methods of outreach have not been fully successful.

**Trial registration:**

Clinical trials.gov, NCT03117842. Registered on 31 March 2017.

**Electronic supplementary material:**

The online version of this article (10.1186/s13063-018-2614-7) contains supplementary material, which is available to authorized users.

## Background

Mobile phones are increasingly being used to enhance the effectiveness of health programs by engaging individuals in discreet and ongoing ways. Mobile phone health interventions, called mHealth, can also improve the availability and quality of operational research data. mHealth interventions have been used successfully in developing countries to collect health data [1, 2], increase access to health knowledge [3–7], and increase medication/appointment adherence [8–11]. But, few mHealth interventions have been rigorously evaluated [6, 12]. There is strong evidence that mobile phone messages can be successfully used to support preventative healthcare [3, 5, 8, 12–15], such as maternal postpartum visit attendance and prevention of maternal-to-child transmission (PMTCT) of HIV in Kenya [16] and HIV prevention in India [17]. There is also evidence that self-report of risk behaviors through a mobile phone is a method of data collection that is as reliable and valid as in-person surveys [18]. Especially for mobile or hidden populations in developing countries, mobile phones may become our most important tool for gathering real-time health information and then linking people to health services [4, 5, 9, 17].

In Cambodia, several successful mobile-phone-based health programs have been introduced in the areas of post-abortion contraceptive use [19], pharmacovigilence [20], diabetes self-management [21], tuberculosis case detection/notification [22], and HIV education [23]. The current evidence base for mobile phones used for health assessment and encouragement of the uptake of services, especially for hard-to-reach populations that face stigma and discrimination in developing countries, is promising, but stronger impact evaluations are needed to understand the full benefits of such interventions.

One important hard-to-reach key population in Cambodia is the growing population of female entertainment workers (FEWs). FEWs are women working in entertainment venues such as karaoke bars, massage parlors, restaurants (as hostesses or singers), or beer gardens [24, 25]. FEWs frequently sell sex, directly or indirectly, to male patrons to supplement their income [24, 25]. By 2013, there were approximately 40,000 FEWs in Cambodia, 24,000 of whom resided in the capital city of Phnom Penh [26]. This group has been increasing since the 2008 passage and implementation of the “Law on Suppression of Human Trafficking and Sexual Exploitation,” which banned brothel-based sex work, more women have moved into indirect sex work based out of entertainment venues.

The influx in the number of FEWs also follows the increase in garment factory jobs that attract young women from poor rural families to migrate to urban areas to earn and remit income to their families in their home villages [24, 27]. Today, the garment factories in Cambodia employ over 700,000 young women [28]. Garment workers endure unsafe work environments [29] and claiming worker rights is fraught with dangers. As a result, more and more young migrant women become involved in alternative work opportunities in the entertainment industry. In addition, urban youth may also be at risk of engaging in sex work. A recent study from Cambodia found that 48% of at-risk female youth across the country reported having been paid for sex in the past year [30].

FEWs in Cambodia are considered at high risk for poor sexual and reproductive health (SRH) outcomes because of their involvement in direct or indirect sex work and limited access to SRH services [24, 30]. Recent studies indicate that HIV prevalence among women working in other entertainment establishments (9.8%) is lower than street-based sex workers (37.3%) and brothel-based sex workers (17.4%), but is still considered a national concern [31]. Recent data showed HIV incidence among FEWs was 9.2% in 2009 [32]. In addition, incidences of *C. trachomatis*, HPV, and *N. gonorrhea* among FEWs are 11.5%, 41.1%, and 7.8%, respectively [33, 34].

Recent surveys on HIV testing rates indicate that 81.7% of FEWs reported ever having had an HIV test, and 52.3% reported having had an HIV test in the past six months [35]. While there have been increases in reported condom use in commercial sex work over the past decade, there may be misreporting of condom use as well as condom failure. Consistent condom use is highly variable depending on the nature of relationship and several other factors [36, 37]. In 2014, our study of 667 FEWs showed that, in the past three months, 63.9% were able to find condoms when needed, and 38.2% used condoms at last sex with non-commercial partners [35]. Consistent condom use among FEWs and non-commercial partners, such as boyfriends or other romantic relationships, in the past three months is estimated to be 20.6–34.1% [33, 35, 38]. Moreover, recent studies have shown that 21.4% of FEWs reported having induced abortions since working in entertainment [31]. Sexually transmitted infections (STIs) are also common among FEWs [32–34].

In Cambodia, government and NGO providers currently offer free and widely available SRH services to FEWs. However, some FEWs experience barriers to using these services such as discrimination by providers. FEWs report a preference for private providers as a result [39]. KHANA, the largest national HIV organization in Cambodia, is currently offering specialized services for FEWs including free distribution of condoms, a “safe space” drop-in center, community-based finger-prick HIV and syphilis testing, accompanied referrals to enrolment of HIV-positive FEWs to pre-antiretroviral therapy (ART) and ART services, the integration of SRH services with HIV services, partner tracing, and PMTCT programming. Increasing utilization of these services by FEWs is a high priority.

The *Mobile Link* intervention is an operational mHealth research project that aims to engage FEWs and link them to the existing high-quality prevention, care, and treatment services in the country. This intervention will consist of theory-based text, i.e. short message service (SMS), or voice messages (VM), that aim to reduce risk behaviors and increase the linkage to and utilization of SRH and other related services among FEWs in Cambodia. In addition, this intervention may help to determine if SMS/VM messaging can be a reliable source of monitoring and evaluation data with this population. The initial operational research project will focus on FEWs as a proof of concept and, if effective, the *Mobile Link* intervention program will be tailored for other key populations.

